### 4.2.2 Secondary outcome

The efficacy of the combination regimens will also be assessed by comparing the treatment groups as follows:

1. Proportion of patients with clinical failure (ETF/LTF) at 14 days of follow-up (Appendix 3)
2. Proportion of patients with parasitological resistance (RI/RII/RIII) at 14 and 28 days of follow-up (Appendix 3) to supplement results of clinical outcome and to facilitate comparison with historical data.
3. Proportion of patients with treatment failure according to new WHO guidelines (ETF/LCF/LPF) at 14 and 28 days of follow-up (Appendix 3).
4. Rate of fever clearance: presence or absence of objective fever (axillary temperature > 37.5C) or patient report of fever on days 1, 2, 3
5. Rate of parasite clearance: proportion of positive vs. negative thick blood smears on day 2 and day 3
6. Change in mean haemoglobin from day 0 to 28
7. Proportion gametocytemic: presence vs. absence of gametocytes on any follow-up thick blood smear; proportion gametocytemic on days 2, 3, 7, 14, 21, and 28.

The safety and tolerability of the combination regimens will be further compared as follows:

1. Incidence of serious adverse events (AEs): proportion of patients experiencing any serious AE in each treatment group during the 28-day follow-up period.
2. Incidence of AEs: proportion of patients experiencing any mild/moderate/severe/life-threatening AEs during the 28-day follow-up period
3. Incidence of AEs by specific sign or symptom during the 28-day follow-up period

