### 6.0 BASELINE EVALUATION AND TREATMENT ASSIGNMENT

### 6.1. Baseline evaluation and procedures:

On Day 0, patients enrolled and assigned study numbers will undergo a complete history and physical examination (Appendix 5 and 6). On day 0, a finger-prick blood sample will be obtained for repeat thick blood smear, thin blood smear, haemoglobin measurement and to save on filter paper for future molecular testing. Because only rapid Giemsa-stained thick smears are typically assessed in the outpatient laboratory, a thick and thin blood smear obtained at enrolment will be stained with 2% Giemsa and read by experienced laboratory technicians who are not involved in direct patient care. Parasite densities will be calculated by counting the number of asexual parasites per 200 leukocytes (or per 500, if the count is <10 parasites/200 leukocytes), assuming a leukocyte count of 8,000/l. A blood smear will be considered negative when the examination of 100 high power fields does not reveal asexual parasites. Gametocytemia will also be determined from thick smears. Thin smears will be used for parasite species identification.

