### FOLLOW-UP EVALUATION AND PROCEDURES

7.1. Follow-up schedule:

Patients will go home on Day 0 and will be asked to return to the clinic for follow-up on Days 1, 2, 3, 7, 14, 21, 28, and any unscheduled day that they feel ill. All patients will be reimbursed the cost of their transport to and from the clinic. Details about the location of the patient’s residence will be obtained and if a subject does not return for a scheduled clinic follow-up appointment, the study personnel shall visit them at home. Patients who return on Day 1 and fail to fulfil the criteria of *P. falciparum* mono-infection with a parasite density of > 2000 parasites/ul and < 200,000 parasites/ul will be excluded from further study and referred to OPD for management. At each repeat visit, temperature will be measured and a focused physical examination will be performed. A finger prick blood sample will be obtained on Days 2, 3, 7,14, 21 and 28 (and any extra day) to repeat thick blood smears and to save on filter paper. Haemoglobin will be re-evaluated either on day 28 or at the time of clinical treatment failure. All thick smears will be assessed for parasite density and presence of gametocytes. Any patient who is suspected of clinical treatment failure after Day 3 will have a repeat thick and thin smear obtained.

Follow-up Schedule

|  | **Day 0** | **Day 1** | **Day 2** | **Day 3** | **Day 7** | **Day 14** | **Day 21** | **Day 28** | **Extra Day** | **When necessary** |
| --- | --- | --- | --- | --- | --- | --- | --- | --- | --- | --- |
| Study medications | X | X | X |  |  |  |  |  |  |  |
| History | X | X | X | X | X | X | X | X | X |  |
| Temperature measurement | X | X | X | X | X | X | X | X | X |  |
| Physical exam | X | X | X | X | X | X | X | X | X |  |
| Neurologic exam (3-arm study only) | X |  |  |  | X | X | X | X | * |  |
| Thick blood smear | X |  | X | X | X | X | X | X | X |  |
| Thin blood smear | X |  |  |  |  |  |  |  |  | CTF after day 3 |
| Filter paper sample | X |  |  | X | X | X | X | X | * |  |
| Haemoglobin | X |  |  |  |  |  |  | X | * | If CTF, on day of failure |
| Assessment for adverse drug event | X | X | X | X | X | X | X | X | X |  |

X = perform this task

* As indicated

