### 7.3. Management of clinical treatment failures:

Patients who are classified as clinical failures (early or late treatment failure, Appendix 3) will be treated with quinine 10 mg/kg orally three times a day for 7 days. Any patient who develops evidence of severe malaria or danger signs during malaria follow-up, will be referred for appropriate treatment with parenteral quinine at the local facility or hospital. Any patient who responds clinically to treatment, but has a positive thick blood smear on day 28 (asymptomatic parasitaemia) will be treated with standard doses of oral quinine. Hemoglobin will be repeated on the day the patient is classified as a clinical treatment failure.

- 1. **Exclusion after enrolment and loss to follow-up:**

Patients will be excluded from the study after enrolment if any of the following occurs:

- 1. Use of antimalarial drugs outside of the study protocol.
  2. Development of concomitant febrile illness that may interfere with outcome classification.
  3. Withdrawal of informed consent.

Patients who fail to attend a follow-up visit and are unable to be located within 24 hours on Days 1-3 or within 48 hours on Days 4-28 will be considered lost to follow-up.

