### 8.2. Analytical plan:

Data analysis will be primarily performed by the project statistician using EPI INFO, SPSS ACCESS and STATA statistical software packages, with additional assistance from members of the UCSF Epi-Center in San Francisco and the University of California, Berkeley, Department of Epidemiology. Primary analyses will be conducted based on intention-to-treat and the primary analysis population will include all randomised subjects fulfilling selection criteria.

Descriptive statistics will be used to summarise baseline characteristics of study patients. Parasite density values will be normalised using logarithmic transformation. All dichotomous variables will be compared between treatment groups using chi-square tests or Fisher’s exact tests. Continuous variables will be compared using t-tests. A p-value of < 0.05 will be considered significant.

Because age is a strong effect modifier in malaria, an age-stratified subgroup analysis for efficacy outcomes is planned. Study subjects will be stratified by age (< 5 years and > 5 years) for analysis of treatment outcome including clinical outcome at 14 and 28 days, and parasitological outcome at 14 and 28 days. Results for the two age groups will be presented independently. After calculating an estimate of association for each of the two age groups, a single adjusted measure of risk difference will be calculated. Other factors that may impact on antimalarial treatment outcome include temperature4 and mean parasite density at presentation ([name], unpublished data). Because a randomised trial is planned, we anticipate that known and unknown confounding factors will be equally balanced between the treatment groups. If by chance, there is an imbalance between the treatment groups for one or more potential confounding variables, adjustment will be made using multiple logistic regression.

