4. **AEs in patients classified as treatment failures** – Formal study follow-up ends when a patient is classified as a treatment failure (ETF or LTF), and patients should be treated with quinine and managed according to good medical practice. Additional follow-up for AEs in patients classified as treatment failures, is not typically indicated, unless the AE is serious, or is felt to be probably or definitely related to the study medications. The Kampala core facility staff should be contacted with any questions about follow-up of AEs in patients with treatment failure.

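### The gametocyte comparison (section 4.2.2, item 7) ignores Day 0 gametocyte status, which is already recorded, and so gives up precision and interpretability; its late-day proportions describe only patients still in follow-up.

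*Protocol*

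**What the plan says.** Protocol section 4.2.2, item 7 sets two gametocyte measures: "presence vs. absence of gametocytes on any follow-up thick blood smear; proportion gametocytemic on days 2, 3, 7, 14, 21, and 28". Neither refers to Day 0 status, and no denominator is given for the day-specific proportions. The item just before it, on haemoglobin, is defined as a change from Day 0.

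Day 0 status is available. Section 6.1, on the enrolment smears, states "Gametocytemia will also be determined from thick smears", and the laboratory record in Appendix 15 (item 46) has a Day 0 column for gametocytes. Carrying gametocytes is not an exclusion under section 5.2.

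On the test, section 8.2 states "All dichotomous variables will be compared between treatment groups using chi-square tests", with Fisher's exact test as the alternative. If one or more potential confounders prove imbalanced, "adjustment will be made using multiple logistic regression". Day 0 gametocytes are not named there.

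On observation time, Appendix 10 (length of follow-up for adverse events, item 4) states "Formal study follow-up ends when a patient is classified as a treatment failure (ETF or LTF". Section 7.1 states "All thick smears will be assessed for parasite density and presence of gametocytes", and also "Any patient who is suspected of clinical treatment failure after Day 3 will have a repeat thick and thin smear obtained".

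**The concern.** A patient who carries gametocytes at enrolment and is still positive on Day 2 counts as an event in the any-smear measure, exactly like a patient in whom gametocytes first appear after treatment. If Day 0 carriage predicts follow-up carriage, an unadjusted test leaves that known source of variation in the error term. The adjustment clause in section 8.2 does not help, because the loss occurs even when carriers are perfectly balanced between arms.

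A second point concerns the late days. Once a patient is classified as a clinical failure, later scheduled smears are no longer part of formal follow-up. The protocol expects failure to differ by arm, so the Day 14, 21 and 28 proportions come from sets of patients selected after randomisation, and selected to different degrees.

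At stake are the power and the reading of one secondary outcome. The primary outcome, the sample size and the primary analysis are not affected.

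**Working it through.** **The plan's own figures.** Section 8.1 gives 160 per group for 15% vs 5% failure and 162 for 10% vs 2% (two-sided alpha 0.05, power 80%). Take n = [1.96√(2p̄(1−p̄)) + 0.8416√(p1(1−p1)+p2(1−p2))]²/d².
- 15% vs 5%: (0.8316+0.3521)²/0.01 = 140.1, so 141.
- 10% vs 2%: (0.6583+0.2786)²/0.0064 = 137.2, so 138.
- Continuity correction, n/4 × [1+√(1+4/(nd))]²: 160 and 162, matching the protocol.
- Dividing by 0.90 for loss to follow-up: 178 and 180, against the stated 180.

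These figures are for clinical failure. The protocol gives none for gametocytes.

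**Inputs for the gametocyte comparison.** From section 8.1: n = 160 per arm and two-sided 0.05. Assumed, because the documents are silent: Day 0 carriage g; new gametocytaemia of 20% vs 10% in Day 0-negative patients; and the share of carriers positive on some follow-up smear (q1 and q2 for the two arms).

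**Formulas.** Arm rates are a = 0.20(1−g)+g·q1 and c = 0.10(1−g)+g·q2, with Δ = a−c. Power ≈ Φ(Δ/SE − 1.96).
- Unadjusted: SE² = [a(1−a)+c(1−c)]/160.
- Stratified by Day 0 status: SE² = [(1−g)(0.16+0.09) + g(q1(1−q1)+q2(1−q2))]/160.

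**Worked case** (g = 10%, q1 = q2 = 80%): a = 0.26, c = 0.17, Δ = 0.09.
- Unadjusted: SE = √((0.1924+0.1411)/160) = 0.0457; Φ(1.971−1.96) = 50%.
- Stratified: SE = √((0.225+0.032)/160) = 0.0401; Φ(2.246−1.96) = 61%.

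**Range, from the same formulas:**

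| Day 0 carriage | Carriers positive again (q1 vs q2) | Arm rates | Unadjusted power | Stratified power |
|---|---|---|---|---|
| 5% | 80% vs 80% | 23% vs 13.5% | 60% | 67% |
| 10% | 80% vs 80% | 26% vs 17% | 50% | 61% |
| 20% | 80% vs 80% | 32% vs 24% | 36% | 50% |
| 10% | 80% vs 60% | 26% vs 15% | 69% | 77% |
| 20% | 80% vs 60% | 32% vs 20% | 70% | 82% |
| 10% | 50% vs 50% | 23% vs 14% | 55% | 58% |
| 20% | 50% vs 50% | 26% vs 18% | 41% | 46% |
| any | 20% vs 10% (Day 0 not predictive) | 20% vs 10% | 72% | 72% |

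**Restricting to Day 0-negative patients instead.** At g = 10%, n = 144 and SE = √(0.25/144) = 0.0417, so power is Φ(2.400−1.96) = 67%. At g = 20%, n = 128 and power is Φ(2.263−1.96) = 62%.

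**Attrition at the protocol's own failure rates.** Up to 160×0.15 = 24 vs 160×0.05 = 8 patients leave before Day 28, so 136 vs 152 remain. In the low-resistance setting 162×0.10 = 16.2 vs 162×0.02 = 3.2 leave, so about 146 vs 159 remain. These are upper limits, because a patient who fails on Day 28 still has the Day 28 smear.

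**What attrition could do.** Assume Day 28 prevalence of 10% in non-failures in both arms and gF in failures. Patients still in follow-up then show no difference, while the all-patient difference is (difference in failure rate)×(gF−0.10). For gF of 10%, 30% and 50% this is 0, 2.0 and 4.0 points at 15% vs 5%, and 0, 1.6 and 3.2 points at 10% vs 2%. If gF were below 10% the sign would reverse.

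**The case against.** **Counting Day 0 carriers is legitimate.** Randomisation balances them, and gametocyte prevalence in all treated patients, including clearance of carried gametocytes, is a sensible outcome. This stands. A reader might infer that the outcome is biased, or that it should be confined to Day 0-negative patients; the documents support neither. Restriction changes the question and can cost power. If carriers clear differently (80% vs 60% still positive), it gives 67% and 62%, against 69% and 70% for the unadjusted comparison. Stratification keeps everyone and still reaches 77% and 82%.

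**Failures are not dropped.** A reader might infer that patients leave the outcome when they fail. For the any-smear measure that is wrong: section 7.1 has every thick smear read for gametocytes, including the one at suspected failure, so these patients count up to and including that day. Only their later observation is cut short. Under section 7.3, patients with parasitaemia but no clinical failure also stay to Day 28.

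**The late-day bias is not established.** A reader might infer that attrition hides a disadvantage of the less effective regimen. That needs failures to carry gametocytes more often, which the documents do not say. Later smears in failures would in any case reflect rescue treatment. Time to first gametocytaemia censored at failure would not cure the problem, because it also discards what follows failure.

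**This could sit in an SAP that is not shown.** That is fair for the denominators. It is less so for the test: section 8.2 fixes unadjusted comparisons and allows adjustment only for chance imbalance, so the proposal improves on a stated method.

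**Conclusion.** The point holds as one of precision and interpretability on a secondary outcome. The planned test leaves out a baseline variable that the trial already records and that should predict the outcome. Under the assumed rates, with 80% persistence in both arms and carriage of 10% to 20%, stratification adds about 11 to 14 percentage points of power (50% to 61%, and 36% to 50%). It also gains where the regimens differ in clearing carried gametocytes (69% to 77%, and 70% to 82%). The gain shrinks to 3 to 5 points at 50% persistence and disappears if Day 0 status predicts nothing. All gametocyte rates are assumptions; only the 160 per arm and the test level come from the protocol.

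On attrition, the documents support one statement: at the expected failure rates, up to 10 percentage points (or 8 in the low-resistance setting) more patients leave the CQ/SP arm than the comparator before Day 28. The Day 14, 21 and 28 proportions therefore describe patients still in follow-up. The direction and size of any resulting bias cannot be derived from the documents.

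**What to change.** 1. In sections 4.2.2 (item 7) and 8.2, make the planned gametocyte comparison stratified by or adjusted for Day 0 gametocyte status, by Mantel-Haenszel or logistic regression, whether or not a chance imbalance appears. A Mantel-Haenszel risk difference would match the adjusted risk difference that section 8.2 already plans across age groups.
2. Report Day 0 gametocyte prevalence by arm. Give results in Day 0-negative patients (new appearance) and Day 0-positive patients (persistence) as supportive.
3. Let the any-follow-up-smear measure carry the comparison between arms, and state that it includes the failure-day smear. Note that failures contribute fewer smears.
4. Present the Day 14, 21 and 28 proportions with their denominators, labelled as describing patients still in follow-up.

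The cost is wording and a few lines of analysis. The Day 0 and failure-day readings are already collected, so no visit, sample or patient is added, and adjustment excludes nobody with a Day 0 reading.

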### 7.2.2. Identification of adverse events:

At each follow-up visit (days 1, 2, 3, 7, 14, 21, 28, and any unscheduled day), study clinicians will assess patients according to a standardized clinical record form (Appendix 14). All signs and symptoms present will be graded as mild, moderate, severe, or life threatening according to examination guidelines (Appendix 6). An AE will be defined as a sign or symptom of untoward medical occurrence arising or increasing in severity compared to the previous day’s record.

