### 8.0 STATISTICAL CONSIDERATIONS

### 8.1. Sample size calculations:

The sample size calculations will be made for each study based on the estimated efficacy of the combination regimens to be studied in the given region. For the purposes of sample size calculation, the risk of clinical failure at 28 days will be the main outcome. If the null hypothesis states that there is no difference in clinical outcome between the treatment groups, we plan to test the alternative hypothesis that treatment with an alternative combination regimen (AQ/SP or AS/AQ) will decrease the likelihood of clinical failure at 28 days of follow-up. Calculations will be made using an α = 0.05 and a statistical power of 80% based on a two-sided test. Allowance will be made for a possible 10% loss to follow-up to ensure that an adequate number of patients complete the study. Based on this, the sample size for the various drug combinations is summarized below:

Sample size for the different drug combinations

| **Presumed level of resistance.** | Resistance to CQ/SP | Resistance to AQ/SP or AS/AQ | Number per group | Number per group adjusted for loss to follow up. |
| --- | --- | --- | --- | --- |
| High resistance community (urban areas) | 15% | 5% | 160 | 180 |
| Low resistance community (rural areas) | 10% | 2% | 162 | 180 |

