### APPENDIX 3. OUTCOME CLASSIFICATION

### Clinical Outcome Classification System

| ACR (Adequate Clinical Response)   - Absence of parasitemia on Day 28, without previously meeting criteria for ETF or LTF - Temperature < 37.5C (Axillary) and no history of fever in last 24 hours on day 28 irrespective of the presence of parasitemia, without previously meeting any of the criteria of ETF or LTF |
| --- |
| ETF (Early Treatment Failure): Days 0, 1, 2, and 3  - Development of danger signs or severe malaria on Days 0-3 in the presence of parasitemia - Parasitemia on Day 2 higher than Day 0 count irrespective of temperature - Temperature > 37.5C (Axillary) on Day 3 in presence of parasitemia - Parasitemia on Day 3 > 25% Day 0 count |
| LTF (Late Treatment Failure): Days 4 To 28  - Development of danger signs or severe malaria on Days 4 to 28 in the presence of parasitemia, without previously meeting any of the criteria of ETF. - Temperature > 37.5C (Axillary) or history of fever in last 24 hours on Days 4 to 28 in the presence of parasitemia, without previously meeting any of the criteria of ETF. |

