**Appendix 5. Guidelines for Grading Patient Symptoms**

|  | **Grade 1**  **MILD** | **Grade 2**  **MODERATE** | **Grade 3**  **SEVERE** | **Grade 4**  **LIFE THREATENING** |
| --- | --- | --- | --- | --- |
| **Subjective fever in the past 24 h** | N/A | Present (Yes) | N/A | N/A |
| **Convulsion** | N/A | N/A | Localized or generalized seizure | Status epilepticus |
| **Headache*** | Mild, no therapy required | Transient, moderate; therapy required | Severe; responds to initial narcotic therapy | Intractable; requires repeated narcotic therapy |
| **Anorexia** | Decreased appetite, but still taking solid food | Decreased appetite, avoiding solid food | Refusing to breast feed, appetite very decreased, no solids or liquids taken (< 2 years < 12 hr; > 2 years < 24 hr) | Refusing to breast feed, appetite very decreased, no solids or liquids taken (< 2 years < 12 hr; > 2 years < 24 hr) |
| **Nausea*** | Mild discomfort; maintains reasonable intake | Moderate discomfort; intake decreased significantly; some activity limited | Severe discomfort; no significant intake; activities limited | Minimal fluid intake |
| **Vomiting** | Transient emesis | Occasional or moderate vomiting | Orthostatic hypotension or IV fluids required | Hypotensive shock or hospitalization required for IV fluid therapy |
| **Abdominal pain*** | Mild | Moderate – no treatment needed | Moderate to severe – treatment needed | Severe – hospitalized for treatment |
| **Diarrhea** | Transient 3-4 loose stools/day | 5-7 loose stools/day | Orthostatic hypotension or > 7 loose stools/day or IV fluids required | Hypotensive shock or hospitalization for IV fluid therapy required |
| **Cough** | Transient – no treatment required | Continuous, requires treatment | Uncontrolled | Cyanosis, stridor, severe shortness of breath |
| **Pruritis** | Pruritis without rash | Pruritic rash, pruritis without rash that disturbs sleep | Mild urticaria | Severe urticaria, anaphylaxis, angioedema |
| **Tinnitus*** | Mild ringing or roaring sound | Moderate ringing or roaring sound | Severe ringing or roaring sound with associated hearing loss | N/A |

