**Length of follow-up for adverse events (See Appendix 14)**

1. **AEs presenting during the 28-day follow-up period** - If a patient with a previously reported AE is still experiencing the AE on Day 28, or if a patient presents with a new AE on Day 28, the Kampala core facility staff should be notified to discuss the plan for further follow-up vs. discharge from the study. Patients with ongoing AEs on Day 28 will be managed according to the following guidelines:
   1. If the AE is “old” (previously reported on Days 0-27) and is < grade 1 (mild), the patient will be managed according to good medical practice and will be discharged from the study. The date of resolution for the AE will be recorded as Day 28.
   2. If the AE is “old” (previously reported on Days 0-27) and is > grade 1, the patient will be followed until the AE resolves, improves, or stabilizes.
   3. If the AE is new, the AE will be reported and the patient will be followed until the AE resolves, improves, or stabilizes.
2. **AEs presenting after Day 28** – If a patient presents with a new AE during a follow-up visit after Day 28, the new AE will be managed according to the following guidelines:
   1. If the AE is serious, and the relationship of the event to study medications is “NONE” or “UNLIKELY”, the patient will be managed according to good medical practice, but the AE will not be reported or followed.
   2. If the AE is serious, and the relationship of the event to study medications is “POSSIBLY”, “PROBABLY” or “DEFINITELY”, the AE will be reported and the patient will be followed until the AE resolves, improves, or stabilizes.
   3. If the AE is not serious, the patient will be managed according to good medical practice, but the AE will not be reported or followed.
3. **Serious AEs** – Any patient who experiences a serious AE should be followed until the AE resolves or improves (< grade 1). Please note that if a patient develops evidence of severe malaria or danger signs, and requires treatment with parenteral quinine +/- hospitalization, the symptoms / signs / laboratory abnormalities leading to the diagnosis of severe malaria will be classified as serious AEs. Although formal study follow-up is typically terminated when a patient is classified as a treatment failure, any patient with severe malaria / danger signs should be followed up to ensure their serious AE has resolved / improved, and data should be recorded on the Serious Adverse Event – Follow-up Form.

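### The safety outcomes do not separate the signs of treatment failure from other adverse events, so the tolerability comparison partly restates efficacy

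*Protocol*

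**What the plan says.** - **Outcomes.** Protocol 4.2.2 lists three safety comparisons over 28 days: any serious AE, the "proportion of patients experiencing any mild/moderate/severe/life-threatening AEs during the 28-day follow-up period", and AEs by specific sign or symptom. None uses the suspected relationship to study drug, and none sets aside events that are part of a treatment failure.
- **AE definition.** Section 7.2.2 states: "An AE will be defined as a sign or symptom of untoward medical occurrence arising or increasing in severity", judged against the previous record. Appendix 10 adds that presumed cause is irrelevant. Section 7.2.3 concedes that mild symptoms are hard to tell from malaria but keeps mild AEs in the analysis.
- **Fever as a graded finding.** In Appendix 5 the row "Subjective fever in the past 24 h" has a single grade, moderate. Appendix 6, Table B, grades axillary temperature from 37.5C.
- **Fever as failure.** In Appendix 3, late treatment failure (LTF) is met by raised temperature or "history of fever in last 24 hours on Days 4 to 28 in the presence of parasitemia". Severe malaria or danger signs with parasitaemia are criteria for early failure (ETF) and for LTF.
- **Severe malaria.** Appendix 10, on length of AE follow-up, says that the findings "leading to the diagnosis of severe malaria will be classified as serious AEs".
- **End of follow-up.** The same part of Appendix 10 ends formal follow-up at ETF or LTF. AEs are then not usually followed unless serious or probably or definitely drug-related.

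**The concern.** Safety and tolerability are study aims alongside efficacy (section 3.0), and section 2.2 sends the data to the Ministry of Health for drug policy. Section 8.1 assumes that CQ/SP fails three to five times as often as the alternatives (15% vs 5%, or 10% vs 2%). If the signs of failure are also counted as AEs, the extra events fall mainly on CQ/SP. A regimen that works better but is less well tolerated could then look equally tolerable, and an equally tolerated one could look better. The outcomes affected are any AE, serious AEs, and the symptom-level counts for fever and for other symptoms that recur with malaria.

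**Working it through.** **1. Does a failure count as an AE?** Take a patient whose Day 7 record shows no fever and who reports fever on Day 14 with parasitaemia. Appendix 3 classifies this as LTF. Appendix 5 grades the fever as moderate. Section 7.2.2 makes it an AE because it is new against the previous record. The second worked example in Appendix 10 confirms this reading: nausea graded 2, 1, 0, 2 over Days 0-3 is an AE on Day 3, although it has only returned to its Day 0 grade. For serious AEs the rule is explicit and no inference is needed.

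**2. The plan's figures.** Section 8.1 states: "Calculations will be made using an α = 0.05 and a statistical power of 80% based on a two-sided test". The high-resistance row reads "High resistance community (urban areas) | 15% | 5% | 160 | 180". The two-proportion formula with continuity correction gives 160 for 15% vs 5% and 162 for 10% vs 2%, as stated (141 and 138 without the correction). On losses the plan says: "Allowance will be made for a possible 10% loss to follow-up". 160/0.9 = 178 and 162/0.9 = 180, against a stated 180 for both. The sample size is not in dispute. It supplies the failure risks used below.

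**3. Model.** Let a be the risk of an AE not due to malaria, f the failure risk, and q the share of failures that add a new AE. With independence, P(any AE) = 1 - (1 - a)(1 - qf). The protocol gives neither a nor q, so both are assumed over a range.

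For q = 1:
- False gap between equally tolerated arms = (1 - a)(f1 - f2).
- Excess harm hidden in the more effective arm = (1 - a)(f1 - f2)/(1 - f2).

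| a | Any AE at 15%/5%, equal tolerability | False gap, 15%/5% | Hidden excess, 15%/5% | Hidden excess, 10%/2% |
|---|---|---|---|---|
| 5% | 19.3% vs 9.8% | 9.5 | 10.0 | 7.8 |
| 10% | 23.5% vs 14.5% | 9.0 | 9.5 | 7.3 |
| 20% | 32.0% vs 24.0% | 8.0 | 8.4 | 6.5 |
| 40% | 49.0% vs 43.0% | 6.0 | 6.3 | 4.9 |
| 60% | 66.0% vs 62.0% | 4.0 | 4.2 | 3.3 |
| 80% | 83.0% vs 81.0% | 2.0 | 2.1 | 1.6 |

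Gaps and excesses are in percentage points.

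**4. Only some failures add an AE.** At a = 10%, with q = 25%, 50% and 75%, the hidden excess is 2.3, 4.6 and 7.0 points (15%/5%) or 1.8, 3.6 and 5.5 points (10%/2%). At a = 60% and q = 50% with 15%/5% failure it is 0.4 × 0.05/0.975 = 2.1 points.

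**5. Effect on a test (q = 1, a = 10%, normal approximation without continuity correction).** With 160 per group and 15%/5% failure, a true 10% vs 19.5% difference in AEs not due to malaria would be detected with about 67% power if analysed alone. In the planned outcome it appears as 23.5% vs 23.5%. With equal tolerability, the chance of a significant difference favouring the more effective arm is about 54% (15%/5%, 160 per group) or 43% (10%/2%, 162 per group).

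**6. Serious AEs.** Assume a drug-related serious AE risk of 0.5% in both arms and 5-20% of failures severe. The observed risks are then 1.2-3.5% vs 0.7-1.5% (15%/5%) and 1.0-2.5% vs 0.6-0.9% (10%/2%), with equal drug safety.

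**7. What the model leaves out.** Follow-up ends at failure, so the arm with more failures has less time in which later AEs can be recorded. This acts against the gaps above. The protocol gives no figures from which to size it.

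**The case against.** **This belongs in the SAP.** Table layout and sensitivity analyses do. But the protocol itself fixes the safety outcomes, the AE definition, the inclusion of mild AEs and the rule for severe malaria, and the overlap follows from those statements.

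**The data to separate events are already collected.** Relationship is graded for moderate and worse AEs, taking malaria status into account. The CRF records the day and reason of failure, and outcome 3 lets fever be read apart. This is true and makes the fix cheap, but no outcome in 4.2.2 uses the relationship grade or the failure record. Outcome 3 does not isolate the other malaria symptoms.

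**Removing failure-day events would remove drug toxicity.** This stands and limits the fix. Repeated vomiting on Days 1-2 is classified as treatment failure (4.4, 6.2). The CRF lists a severe AE forcing a treatment change on Days 0-2 as a reason for failure. Danger signs in Appendix 13, such as vomiting and lethargy, overlap the expected drug events in Appendix 12.

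**Stronger readings do not hold.**
- A reader might infer that recurrent malaria is itself an AE. No passage says so; only its signs and symptoms count.
- A reader might infer that every failure adds an AE. ETF on parasite count alone needs no new symptom, and fever that persists is not new. One sentence in Appendix 10 compares with Day 0 rather than the previous record. On that wording much recurrent fever would not count, since entry requires fever or a history of it. Section 7.2.2 and the worked example favour the previous record, but the two wordings should be reconciled.
- A reader might infer that the bias always runs against CQ/SP. Curtailed follow-up after failure acts the other way.

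**Conclusion.** The concern holds in limited form. Under the stated rules, febrile late failures that follow an afebrile record also enter the AE count, and the signs of severe malaria enter the serious-AE count. The safety comparison is therefore tied to efficacy and can mask or mimic a tolerability difference.

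At 15% vs 5% failure, the distortion is about 9-10 points at 5-10% background AE risk and about 2-4 points at 60-80%. These figures assume that every failure adds an AE and that AEs not due to malaria are independent of failure. They shrink if only some failures add one. A high background is plausible for the any-grade outcome because mild events count. The net sign is not fixed, because lost follow-up after failure acts in the opposite direction. These are secondary outcomes, but they serve a stated aim, so the change is worth making.

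**What to change.** In 4.2.2, keep the all-event outcomes as stated and add a prespecified parallel comparison of AEs and serious AEs:

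- Leave out signs and symptoms first recorded on the day a patient meets the ETF or LTF criteria with parasitaemia. Show them on a separate line labelled malaria treatment failure.
- Keep in the safety count failures recorded for repeated vomiting on Days 1-2 or for a severe AE requiring a change of treatment, and any event graded possibly, probably or definitely related to study drug.
- Because follow-up ends at failure, also report AEs over a common early window fixed in advance, or per time at risk up to failure.

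Recording and reporting of events do not change. Failure day and reason are already on page 4 of the clinical record form. Vomiting failures have no tick box of their own and must be identified from the specified criteria and the symptom record. Mild events carry no relationship grade, so they would be allocated by day and reason of failure.

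The cost is a few lines of protocol wording and one extra table. Some misallocation between drug and malaria events will remain, and the retained all-event version shows how much depends on it.
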